### Design and randomization procedure

The TEG-CABG trial is a prospective open label, randomized clinical trial with blinded evaluation of the primary endpoint (graft patency evaluation by 320 slice-MSCT). Figure
1 shows a flowchart of the study.

**Figure 1 F1:**
[figure not shown]
Study flow chart.

The study nurse, utilizing the sealed envelope technique, randomizes 250 TEG-Hypercoagulable (TEG MA >69 mm) patients on the day before CABG, allocating 125 patients to the interventional group (receiving clopidogrel for three months and lifelong aspirin) and 125 TEG-Hypercoagulable patients to a control group (receiving lifelong aspirin only).

TEG, Multiplate aggregometry and routine blood samples are obtained the day before surgery, on Day 4 after CABG, and at three months postoperatively.

MSCT is conducted at three months after surgery.

### Surgical procedures

All CABG procedures are performed through median sternotomy. At our institution approximately 97% of CABG procedures are performed on-pump with cardiopulmonary bypass and extracorporal circulation (ECC). Patients on ECC are heparinised to maintain an acquired coagulation time (ACT) above 480s, and this is reversed with protaminesulphate (1:1) after finalization of ECC. All patients on ECC receive a total of four grams tranexamic acid during surgery.

The left internal mammarian artery (LIMA) is the preferred conduit for anastomoses to the left anterior descending artery (LAD), for all other anastomoses SVG conduits are preferred.

There is no specific team assigned or any restrictions of cardiac surgeons and/or anesthetists to perform procedures on patients in this trial.

### Perioperative anticoagulation

Routinely, aspirin and clopidogrel are discontinued five days before surgery. In patients with acute coronary syndrome 40 mg of Clexane (enoxaparin- a low-molecular-weight heparine (LMWH)) twice daily or 2.5 mg of Arixtra (Fondaparinux) once daily is administered subcutaneously until the day before surgery. After surgery, only off-pump patients received Clexane 40 mg s.c. twice daily until discharged from hospital, all other patients do not receive LMWH after CABG.

### Description of medical intervention

Aspirin 75 mg is restarted within 24 hours of surgery, in accordance with the current recommendations from ECS/EACTS
[13]. In the intervention group clopidogrel is started at Day 2 after surgery, with a 300 mg oral bolus to achieve greater initial platelet inhibition
[24,25]. Thereafter, clopidogrel therapy is continued with a daily dose of 75 mg for 90 days. Our study is the first study in CABG patients to utilize initial oral bolus of 300 mg clopidogrel. Greater loading doses of clopidogrel (that is, 600 mg) were not utilized due to bleeding concerns - in particular GI bleeding - in the postoperative setting, expressed by the cardiac surgeons at our institution.

Patients will receive study medication (clopidogrel) from the study nurse for the whole study period. At three months the patients are requested to bring in their remaining medication, so compliance can be assessed.

### Outcome measures

Primary:

Graft patency assessed at three months by MSCT will be significantly improved in TEG-Hypercoagulable patients allocated to dual antiplatelet therapy with clopidogrel and aspirin as compared to aspirin alone.

Secondary:

1. TEG-Hypercoagulable patients will suffer fewer thromboembolic events (that is, MI, stroke, pulmonary embolism, gastrointestinal ischemia, deep vein thrombosis) or cardiovascular death when on clopidogrel and aspirin vs. aspirin alone.

2. Assess if the degree of surgically induced hypercoagulability itself is an independent factor of graft occlusion, thromboembolic events and death.

3. High on-treatment platelet reactivity in spite of Aspirin and/or clopidogrel treatment, as evaluated by Multiplate aggregometry, increases the risk of thromboembolic events after CABG surgery.

All outcome measures will be evaluated at three months postoperatively.

### Thrombelastography (TEG)

Until recently, detection of platelet hyper-reactivity demanded sophisticated and time consuming assays. With the modernization and computerization of the TEG methodology, it has gained more clinical interest in specialities beyond cardiac and liver surgery, in which TEG analysis has been used to guide transfusion regimens since the 1980s
[26]. TEG measures kinetics of clot formation, clot strength, platelet function and fibrinolysis, and thus provides a global picture of the patient’s hemostatic ability and the viscoelastic properties of the clot
[26,27]. The analysis is performed on whole blood, in contrast to routine plasma-based coagulation tests
[26]. For TEG-analysis, whole blood is collected in a 3.2% trisodium citrate vacutainer (Greiner Bio-One, Kremsmünster, Austria) and analyzed within 90 minutes after collection by use of a computerized TEG coagulation analyser (TEG model 5000, Haemoscope Corporation, Niles, IL, USA), but not earlier than 30 minutes after collection.

In the TEG analyser, whole blood is incubated in a heated cup (37°C). Within the cup a torsion wire, which can monitor movement, is suspended. In our series we utilize kaolin as a potent initiator of coagulation other activators of coagulation can be used
[23]. The cup starts rotation, and as fibrin forms between the cup and the pin, the rotation is transmitted from the cup to the pin, and the movement of the pin is registered by a computer and the TEG trace is generated
[26,27]. The TEG trace graphically depicts different stages of the hemostatic process; clotting time, kinetics, strength and lysis (*See Figure
2)
[26,27]. The TEG maximal amplitude (MA) depicts the maximal strength of the clot, and MA values above or equal to 69 mm are diagnosed TEG-Hypercoagulable, according to the manufacturer.

**Figure 2 F2:**
[figure not shown]
TEG tracing.

### Multiplate aggregometry

Because of the generation of thrombin secondary to the kaolin (a very potent initiator of coagulation) activation in the TEG assay, the effects of antithrombotic agents such as aspirin (acetylsalicylicacid), non-steroid anti-inflammatory drugs (NSAID), and ADP-receptor inhibitors, such as clopidogrel, cannot be evaluated. Therefore, the effects of aspirin and clopidogrel on platelet inhibition are evaluated by Multiplate impedance aggregometry (Multiplate, Dynabyte Medical, Munich, Germany). The assay consists of two silver-coated copper electrodes immersed in a whole blood sample
[28]. The assay is based on the principle that platelets are non-thrombogenic in a resting state. Upon admission of specific receptor agonists, the platelets will begin to adhere to the electrodes, if the receptors are not blocked by medication. As the platelets adhere to the electrodes, the resistance between the electrodes will increase and the impedance is registered by a computer
[28]. If addition of ADP to a clopidogrel-treated patient sample does not trigger any significant adherence of platelets to the electrodes, this means the drug is successfully blocking the ADP-receptors. If addition of ADP does trigger platelet adhesion, the patient’s ADP receptors are not successfully blocked by clopidogrel. The results of this assay are shown to correlate with the development of thrombotic complications in PCI patients
[21]. This assay has been validated against light transmission aggregometry, which is the “gold standard” in platelet aggregation assays
[28].

In the present study, we use the following platelet agonists: ADP (testing for clopidogrel effect), ASPI (arachnoid acid, testing for aspirin effect) and TRAP (thrombin receptor-activating peptide, testing for maximum response of platelets)
[28].

### Multislice computed tomography (MSCT)

MSCT technology is rapidly evolving in cardiac imaging. MSCT allows for assessment of cardiac structures with high spatial and temporal resolution. MSCT with 16-slice and 64-slice scanners has been validated for assessing graft patency after CABG
[29-31]. Radiation exposure with the evolvement of scanners and scanner software is brought to a minimum, and is now comparable with the radiation exposure of a standard cardiac angiography
[30]. The first 25 patients were scanned with a 64-slice scanner (Toshiba Aquilion 64, Tokyo, Japan); due to an upgrade of the scanner, the rest of the patients included are scanned using a 320-slice scanner (Toshiba Aquilion ONE, Tokyo, Japan). The scanning protocol is as follows: gantry rotation time 350 ms, detector collimation 0.5 x 320. Tube voltage and current are chosen based on the patient’s body mass index ranging between 100 and 120 kV, and mA between 280 and 500. An intravenous contrast media (Visipaque 320 mg I/ml, GE Healthcare, Buckinghamshire, UK) is infused using a flow rate of 6 ml/s followed by a saline chaser. The contrast dye volume used is individually calculated according to patient body mass index (100 to 130 ml). Image interpretation is performed using commercially available software (Vitrea, version 3.0.1, Vital Images, Minnetonka, Minnesota, USA). Grafts are evaluated by two experts in cardiac MSCT these are blinded to patients coagulation and randomization status in the trial.

### Sample size

All patients receive a pedicled left internal thoracic artery graft at our institution; therefore, every patient on average will receive an additional two SVGs. Graft patency for SVGs is approximately 90% after one year. Under the assumption that TEG-Hypercoagulable patients have a lower SVG patency of 80%, and that dual antiplatelet therapy will raise the graft patency of these patients to the rate in uncomplicated patients (90%), calculations based on the Fischer exact test with 80% power and 5% significance level, show the following:

#### ***Improvement of graft patency from 80% to 90%: 219 grafts per group***

With an average of 2 SVGs per patient; 219/2 = 110 patients in each group.

We will include 125 patients in each group to account for “drop-outs” and be able to detect at a significance level of 5% or better.

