### Data and statistical analysis

Results will be included in the final analysis from patients who have complied with correct intake of study medicine. Patients, who fail to do so, will be excluded. Patients, who die during the study period, will be included in a survival analysis. Patients who must discontinue study medication due to a serious adverse event (SAE) will be followed closely until their condition is resolved and relevant treatment is completed. SAEs will be reported to the local health authorities.

Interim analysis will be conducted when 100 TEG-hypercoagulable patients have been enrolled and undergone three-month MSCT.

For categorical variables, χ^2^ tests or Fisher’s exact test will be used as appropriate. For continuous variables, analysis will be performed with the two-sample t-test, after ensuring normal distribution of the data. Data with no normal distribution will be analyzed with the Wilcoxon’s rank-sum test. *P*-values below 0.05 will be statistically significant. Multivariate analyses will be performed, including both demographic and procedural confounding factors. Survival analysis will include a Kaplan-Meyer plot.

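### The sample size counts a patient's two vein grafts as independent, so the stated 80% power is derived for zero within-patient correlation only

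*Protocol article*

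**What the plan says.** The protocol article's Sample size section assumes vein graft patency of 80% in hypercoagulable patients on aspirin and 90% on dual therapy, with "calculations based on the Fischer exact test with 80% power and 5% significance level". The result is "Improvement of graft patency from 80% to 90%: 219 grafts per group". Grafts become patients in one step: "With an average of 2 SVGs per patient; 219/2 = 110 patients in each group". The final increase has its own stated reason: "We will include 125 patients in each group to account for" drop-outs.

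The unit of randomisation is the patient. Under Design and randomization procedure, the study nurse randomises 250 patients, "allocating 125 patients to the interventional group" and 125 to control.

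For categorical variables, Data and statistical analysis says that chi-square tests or Fisher's "exact test will be used as appropriate". It adds multivariate analyses for demographic and procedural confounders. The article does not mention that grafts are nested within patients, and gives no correlation or design effect.

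**The concern.** Dividing 219 by 2 is valid only if the second graft in a patient carries as much new information as a graft in another patient. The trial's own reasoning points the other way. The Background links high on-treatment platelet reactivity, measured per patient, to early vein graft thrombosis. The second secondary outcome asks whether the degree of surgically induced hypercoagulability, also measured per patient, is an independent factor in graft occlusion. If such patient-level factors matter, two grafts in one patient tend to stay open or close together, and the ICC is positive.

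Two things are at stake. The planned number of patients then carries less information than the calculation credits, so a test that respects the clustering has less power than its graft count suggests. And a graft-level test that ignores the clustering uses standard errors that are too small, which pushes up the false-positive rate.

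**Working it through.** **Inputs from the article.** Patency 80% against 90%; 80% power; 5% level; on average 2 vein grafts per patient; 110 patients per group before drop-outs and 125 after. Sidedness is not stated; two-sided reproduces the figure.

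**Assumed.** ICC of 0.1, 0.2, 0.3 and 0.5 (none is given), and exactly two grafts in every patient.

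**1. Reproduce the plan's figure.** Uncorrected n = [1.96·√(2·0.85·0.15) + 0.8416·√(0.8·0.2 + 0.9·0.1)]² / 0.1² = 199.0. With the continuity correction, n = (199.0/4)·[1 + √(1 + 4/(199.0·0.1))]² = 218.5, so 219 grafts per group. Then 219/2 = 109.5, rounded up to 110. Exact Fisher power with 219 independent grafts per group is 81.2%. The figure reproduces exactly with independent grafts and contains no hidden allowance for clustering.

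**2. Effective number of grafts.** With two grafts per patient the design effect is 1 + (2 − 1)·ICC = 1 + ICC. For 110 patients, n_eff = 220/(1 + ICC).

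**3. Power of a test that allows for clustering, at n_eff.**
- Pooled z: Φ{[0.1·√n_eff − 1.96·√(2·0.85·0.15)] / 0.5}. At ICC 0.2, n_eff = 183.3 and power = Φ[(1.354 − 0.990)/0.5] = 76.7%.
- Wald test on the log odds ratio: ln 9 − ln 4 = 0.811, variance (1/0.16 + 1/0.09)/n_eff = 17.36/n_eff. At ICC 0.2, SE = 0.308 and power = Φ(0.811/0.308 − 1.96) = 75.0%.
- Fisher basis: exact Fisher power at n_eff.

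| ICC | n_eff per group (110 patients) | Wald to pooled z, 110 evaluable | Fisher basis, 110 evaluable | Wald to pooled z, 125 evaluable |
|---|---|---|---|---|
| 0.1 | 200 | 79–80% | 77% | 83–85% |
| 0.2 | 183 | 75–77% | 73% | 80–82% |
| 0.3 | 169 | 72–73% | 69% | 77–79% |
| 0.5 | 147 | 65–67% | 62% | 71–73% |

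**4. Patients needed on the plan's own basis.** 219·(1 + ICC)/2 gives 121, 132, 143 and 165 per group before drop-outs. If all 125 per group were evaluable, 250 grafts would cover a design effect of 250/219 = 1.14, an ICC of about 0.14.

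**5. Type I error of an unadjusted graft-level test.** With patency p in both arms, both grafts of a patient are open with probability p² + ICC·p(1 − p). At p = 0.8 and ICC 0.3 that is 0.64 + 0.048 = 0.688; exactly one is open with probability 0.224 and neither with 0.088. Exact enumeration for 110 patients per group and p = 0.8:

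| ICC | Chi-square | Fisher |
|---|---|---|
| 0 | 5.0% | 3.8% |
| 0.1 | 6.1% | 4.8% |
| 0.2 | 7.3% | 5.8% |
| 0.3 | 8.5% | 6.9% |
| 0.5 | 10.9% | 9.0% |

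The power of the unadjusted Fisher test falls less, from 81.1% at ICC 0 to 79.0% at 0.2 and 76.5% at 0.5, because it is no longer a 5% test at those correlations.

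**The case against.** Several objections have weight.

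- **The graft-level test is inferred.** Data and statistical analysis gives a general list for categorical variables and never says that the primary endpoint is tested graft by graft. That reading comes from the Fisher calculation on grafts. An analysis plan not shown here could specify a clustered model. This stands, and makes the type I error part conditional. It does not rescue the sizing: a clustered model protects the 5% level but cannot supply information that the grafts do not carry.
- **Fisher's test is conservative.** A reader might infer that the false-positive rate must exceed 5%. For chi-square it does at every positive ICC examined. Fisher is still at 4.8% at ICC 0.1 and passes 5% only above roughly that value.
- **The loss may be small.** A reader might infer that 80% power and a 5% level are certainly missed. With a large-sample clustered test, about 80% survives at ICC 0.1. With all 125 evaluable it survives to about 0.2, but that spends the whole drop-out margin, and the same section also removes patients who do not take study medication correctly.
- **The correlation may be modest.** All randomised patients have a maximum amplitude above 69 mm, and non-compliers are excluded; both narrow the differences between patients. A surgeon is shared across patients as well as within them. A positive ICC remains plausible, but its size is not established.
- **The arithmetic is right.** It is: 219 and 110 both reproduce. The fault is the unit counted, not the calculation.

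**Conclusion.** The point holds for the sample size. It rests on the article's text alone: grafts are counted, patients are randomised, no design effect is applied, and the margin to 125 has another purpose. The 80% figure is derived under zero within-patient correlation, an assumption at odds with the trial's premise of patient-level occlusion risk.

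How much is lost depends on an ICC that the article does not give. With 110 evaluable per group and a large-sample clustered test, the loss is negligible at 0.1, about 3 to 5 points at 0.2, 7 to 8 at 0.3 and 13 to 15 at 0.5. The figures assume two grafts in every patient. The article gives two only as an average, and unequal numbers raise the design effect; with an assumed coefficient of variation of 0.4 it is 1.26 instead of 1.20 at ICC 0.2.

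Inflation of the type I error follows only if the primary comparison is an unadjusted test on grafts. The sizing implies this, but the article does not state it.

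**What to change.** Keep 250 patients and make two changes.

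1. Name a primary analysis of graft patency with the patient as the cluster: logistic GEE with robust standard errors, or logistic regression with a patient random intercept. This replaces any unadjusted graft-level chi-square or Fisher test. If the full analysis plan already does so, only the article's description needs aligning.
2. Replace the unconditional 80% with power over a stated ICC range, computed for the analysis chosen. For a large-sample clustered test with 110 evaluable patients per group, the approximations above give 75–77% at ICC 0.2 and 72–73% at 0.3. The Fisher-basis values of 73% and 69% should not be quoted for a GEE or mixed model, because they carry Fisher's conservatism.

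The cost is a less favourable power statement and slightly more analysis work. No extra patients or data are needed.

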### Data collection

Preoperatively, during surgery, at Days 3 to 5 after surgery, at discharge and then again three months after surgery, data are collected and entered in the case report form (CRF). The following data will be collected: demographic data, past medical history with special emphasis on cardiac and thromboembolic disease and medication. Intraoperatively data will also be included, this includes a description of the quality of SVGs. In-hospital events, such as MI, stroke and bleeding complications, will be registered. Throughout the study period, blood component transfusion requirements will be registered. The data are transferred from the CRF to a secure database by the project coordinator. The local data safety set-up has been approved of the Danish Data Protection Agency.

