### Antiplatelet therapy after CABG

Antiplatelet therapy with aspirin is well established after CABG. Graft occlusion rates in the 1980s were reduced from 20 to 30% in the first year after surgery to 10 to 15%, if aspirin therapy was restarted 6 to 24 hours after surgery
[3]. Clopidogrel is a thienopyridine antiplatelet agent that inhibits adenosine diphosphate (ADP)-receptors on the platelet surface (P2Y12 receptors), thereby reducing platelet activation and aggregation
[10]. Dual antiplatelet therapy with clopidogrel in addition to aspirin is well established in the treatment of acute coronary syndromes and in PCI patients, and has been shown to significantly reduce cardiovascular events and death as compared to aspirin treatment alone in these patients
[10-12]. However, these studies have also reported that dual antiplatelet therapy significantly increases bleeding risk
[10-12].

The role of dual antiplatelet therapy after CABG is still not clear. Current guidelines from the European Society of Cardiology (ECS) and European Association of CardioThoracic Surgeons (EACTS) recommend dual antiplatelet therapy in acute coronary syndrome patients after CABG
[13]. These recommendations are primarily based on the “Clopidogrel in Unstable angina to prevent Recurrent ischemic Events” (CURE) and “Clopidogrel Versus Aspirin in Patients at Risk of Ischemic Events” (CAPRIE) trials
[12,14]. It should be noted though, that the subgroup study of the CURE trial failed to demonstrate any beneficial effect of clopidogrel after CABG
[14]. Furthermore, the CAPRIE investigators performed a subgroup analysis of patients who have had prior cardiac surgery, but did not stratify for different types of procedures (valve surgery, CABG and so on) and also did not take time from surgery to inclusion in the study (up to years) into consideration
[12]. Consequently, these data do not support the routine use of clopidogrel in addition to aspirin after CABG in patients with acute coronary syndrome undergoing surgical revascularization, and this has been corroborated by a recent Cochrane review
[15].

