## Discussion

The evidence for clopidogrel in addition to aspirin after CABG is divergent, although most studies have not been able to demonstrate any beneficial effect of dual antiplatelet therapy. Meanwhile, emerging evidence from observational studies has demonstrated a significantly higher thromboembolic risk in both PCI and CABG patients that are TEG-Hypercoagulable. The TEG-CABG trial is the first randomized trial to investigate preoperatively TEG-Hypercoagulable CABG patients. The rationale being that this is a patient population with a heightened thromboembolic risk (including graft occlusion) due to the hypercoagulability, but, hence, also is at low risk for bleeding on dual antiplatelet therapy. We hypothesize that this subgroup of CABG patients will benefit the most on a dual antiplatelet regimen both in regards to SVG patency and thromboembolic complications in general.

Examining hemostatic ability and status before and after surgery/intervention with TEG, we believe will be the future for postoperative thromboembolic risk evaluation. Including Multiplate aggregometry measurements in our trial will also help elucidate if resistance measurements after cardiac surgery can help better tailor antiplatelet regimens. These points become even more important as the patients referred to cardiac surgery get older and have more co-morbidities, and, hence, have limited physiological reserves, where graft occlusions and even small thromboembolic episodes can have detrimental effects on overall health and survival.

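### Bleeding, the recognised harm of dual therapy, is not a named outcome, and bleeding complications are listed for registration only in hospital although clopidogrel runs for 90 days

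*Protocol article*

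**What the plan says.** The Background (Antiplatelet therapy after CABG) reports from trials in other cardiac populations that "dual antiplatelet therapy significantly increases bleeding risk". Under Description of medical intervention, larger loading doses "were not utilized due to bleeding concerns - in particular GI bleeding - in the postoperative setting". Table 1 excludes patients with a past peptic ulcer or current bleeding. The Discussion nevertheless builds part of the rationale on the view that the hypercoagulable patient "also is at low risk for bleeding on dual antiplatelet therapy".

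Outcome measures gives the primary outcome as "Graft patency assessed at three months by MSCT will be significantly improved in TEG-Hypercoagulable patients". The first secondary outcome begins "TEG-Hypercoagulable patients will suffer fewer thromboembolic events" and adds cardiovascular death. The second concerns hypercoagulability induced by surgery, and the third concerns platelet reactivity on treatment. All are assessed at three months. Bleeding appears in none of them.

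On exposure: "Thereafter, clopidogrel therapy is continued with a daily dose of 75 mg for 90 days". On collection: "In-hospital events, such as MI, stroke and bleeding complications, will be registered". The next sentence of Data collection registers blood product transfusion for the whole study period, and the section also provides for a three-month CRF entry. Data and statistical analysis has SAEs reported to the authorities, follows patients who stop study drug for an SAE until resolution, and restricts the final analysis to patients who took study medicine correctly.

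**The concern.** The article says its results should help clinicians tailor antiplatelet therapy after bypass surgery. That use needs a bleeding estimate from the same patients over the same treatment period as the patency result. As printed, the outcome list is about efficacy or prognosis only. The one window stated for bleeding complications closes at discharge, while most of the treatment is taken at home. Followed as written, the trial would yield no prespecified between-arm bleeding result for the full treatment period. The low-bleeding statement in the Discussion would then go unexamined in the population to which it is applied.

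The complier rule may add to this. A patient who stops clopidogrel because of a bleed has not completed the study medicine and could be dropped from the final analysis, in one arm only.

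**Working it through.** **The plan's own figure.** The only sample-size figure is for patency: 80% versus 90%, 80% power, 5% significance (Sample size). The two-sided normal approximation gives n = [1.96·√(2·0.85·0.15) + 0.8416·√(0.80·0.20 + 0.90·0.10)]² / 0.10² = (0.990 + 0.421)² / 0.01 ≈ 199. With the continuity correction, n = (199/4)·[1 + √(1 + 4/(199·0.10))]² ≈ 219 grafts per group, as stated. The figure reproduces, but it says nothing about bleeding.

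**What is captured, and when**

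| Item | Window stated | Named outcome? | Between-arm comparison stated? |
|---|---|---|---|
| Bleeding complications | In hospital | No | No |
| Transfusion | Whole study period | No | No |
| SAEs | Not limited to hospital | No | No |
| MI, stroke | In hospital (Data collection); three months (Outcome measures) | Yes | Yes |

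MI and stroke share the in-hospital sentence but are also three-month outcomes. Bleeding has no such second mention.

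**Share of exposure outside the in-hospital window.** Inputs: clopidogrel starts on Day 2 and lasts 90 days (Description of medical intervention). Discharge day d is assumed, because the article gives none. Days in hospital on drug = d − 2; days after discharge = 90 − (d − 2).

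| Discharge day (assumed) | In hospital on drug | After discharge | Share after discharge |
|---|---|---|---|
| 5 | 3 | 87 | 97% |
| 7 | 5 | 85 | 94% |
| 10 | 8 | 82 | 91% |
| 14 | 12 | 78 | 87% |

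Counting the bolus day separately shifts each row by one day at most.

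**What a bleeding outcome could deliver.** With 125 patients per group and a two-sided 5% level, exact Fisher power under assumed three-month bleeding rates is:

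| Assumed rates | Exact power |
|---|---|
| 2% vs 4% | 7% |
| 3% vs 6% | 12% |
| 5% vs 10% | 23% |
| 5% vs 15% | 70% |

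For 5% versus 10%, the half-width of a 95% interval for the difference is 1.96·√(0.05·0.95/125 + 0.10·0.90/125) = 1.96·√0.0011 ≈ 0.065, or about 6.5 percentage points. The outcome would therefore bound the excess without testing a modest one reliably.

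**The case against.** The best reply is that the safety data are less thin than the quoted sentence suggests. Transfusions are registered throughout, SAEs are reported, and a three-month CRF entry exists. The in-hospital sentence gives examples and cannot be exhaustive, since several components of the first secondary outcome are missing from it. A journal article condenses the protocol, so the full document may record bleeding at three months. The general tests for categorical variables could also be applied to whatever bleeding data are collected.

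Much of this stands, and it rules out four stronger readings that a reader might infer:

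- That bleeding after discharge goes unrecorded. Bleeding that leads to transfusion or is an SAE has a stated route. The gap is bleeding that is neither.
- That MI and stroke are also followed only in hospital. Outcome measures places them at three months.
- That patients who stop for bleeding will be excluded. The article treats stopping for an SAE in a separate sentence and does not say that these patients leave the analysis. It also does not say that they stay, so the most that can be said is that they could be dropped.
- That the trial is set up to declare benefit while ignoring harm. No decision rule says so.

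The reply does not meet the core point. The outcome list is given as the trial's primary and secondary outcomes, not as an extract, and the in-hospital window is stated rather than left open. Neither transfusion nor SAEs is an outcome or has a stated comparison. The possible three-month record is conjecture on the text available.

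**Conclusion.** The point holds in limited form. Bleeding is acknowledged as the harm of the tested regimen but is not a named outcome, and bleeding complications have only an in-hospital window against 90 days of clopidogrel. Under an assumed discharge on day 5 to 10, 91% to 97% of treatment days fall outside that window; at day 14 the share is still 87%. These shares measure uncovered treatment time, not the proportion of bleeds missed, which the article gives no means to estimate and which transfusion and SAE records would reduce.

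The patency analysis is unaffected. What is weakened is the step from a patency result to advice on treatment. A bleeding outcome would show the rate and the excess in hypercoagulable patients. It could not show that their risk is lower than that of other bypass patients, because only hypercoagulable patients are randomised. The change should be made, but its absence does not invalidate the trial.

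**What to change.** 1. Under Outcome measures, name bleeding to three months as a safety outcome, using a published bleeding definition chosen before the data are compared by arm.
2. At the existing three-month visit, record bleeding since discharge with the same CRF questions in both arms. This matters more because treatment is open label.
3. Report it by arm in all randomised patients, whatever their compliance, with the difference and a 95% confidence interval. State that patients who stop study drug for an SAE remain in this analysis.
4. Show bleeding from Day 2, when clopidogrel starts, separately from earlier operative bleeding. Randomisation is the day before surgery, so a single count from randomisation would mix in bleeding that occurs before the arms differ in treatment.
5. Present it alongside the transfusions already collected.

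Cost: a few CRF fields at a planned visit and one safety table, with no change to treatment or sample size. There are two drawbacks. With 135 patients already randomised at publication, those past three months can be covered only from records or by retrospective questioning, and this should be marked in the report. The result will also be an estimate, with about 23% exact power for an assumed 5% versus 10%, and should be described as such.
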